### 2.4. Interventions

#### 2.4.1. Cognitive Training

Vektor Cognition Matters (https://cognitionmatters.org/, accessed on 5 October 2021) [34,71] is a challenging open-source and age-based training software program that is designed to support and improve the learning of math in children and adolescents. Vektor consists of several domain-specific (numerical abilities) and domain-general tasks (working memory, mental rotation, and logical reasoning) that are automatically and equally alternated for 20 min. As an adaptive training program, it is calibrated to each individual’s performance.

#### 2.4.2. Transcranial Random Noise Stimulation

Participants in the active tRNS groups will receive 0.75 mA (±0.375 mA) of tRNS (100–500 Hz) to their bilateral dlPFCs (Frontal Group) or bilateral PPCs (Parietal Group) via 2 saline-soaked 25-cm^2^ sponges, placed over F3/F4 or P3/P4, respectively, per the International 10–20 System (Figure 2). The current will be delivered by a BrainStim stimulator (E.M.S. s.r.l.; Bologna, Italy) for 20 min per session, as in previous tRNS protocols [62,63,64,65,66,72,73] and in transcranial direct current stimulation (tDCS) [74,75,76,77] in pediatrics. As in earlier tDCS studies [74,75,76,77], a low dose (1/8 of an inch) of gel cream will be applied to the sponge’s surface to reduce the likelihood of irritation due to electrical stimulation. The impedance of the electrodes will be checked before and during the application of tRNS to ensure that it remains below 10 kΩ.

To control for any placebo effects, participants in the Sham Group will undergo the same procedures as those in the active groups (Frontal Group, Parietal Group), including the same electrode placement, actual placement of electrodes, and time for powering up the tRNS equipment (30 s). Other than this brief stimulation, participants who are randomized to sham tRNS will not receive active stimulation (0 mA) during the remainder of the session. All children will be blinded to the stimulation conditions. See Figure 2.

### 2.5. Outcome Measures

As described, the outcome measures will be presented to each participant individually at T0, T1, and each follow-up (T2 and T3) in a quiet room in random order to control for the effects of fatigue. The outcome measures will include arithmetic, neuropsychological, self-administered, and parental psychological questionnaires and electrophysiological measures.

#### 2.5.1. Arithmetic Measures

Battery for Developmental Dyscalculia. The primary outcome of the study will be the Number Line subtest of BDE-2 [70]. BDE-2 [70] is a standardized clinical battery that is usually adopted in Italy for evaluating numerical cognition in children between the third grade of primary school to the third grade of secondary school. The battery encompasses several subtests that, in turn, are divided into three main quotients: number, calculation, and number sense and a comprehensive index of math abilities, the MTq. Higher scores indicate better outcomes and will be considered as an improvement.

Tempo Test Rekenen (TTR). TTR [78] measures the ability of children to correctly answer with no overt signs of calculations but automatically retrieving arithmetic information from long-term memory. The test consists of 200 written arithmetic number facts, divided into 5 subtests: addition (e.g., “2 + 3 = _”), subtraction (e.g., “8 − 3 = _”), multiplication (e.g., “5 × 9 =_”), division (e.g., “15 : 3 =_”), and mixed facts (e.g., “2 + 1 =_”; “2 − 1 =_”; “2 × 5 =_”; “4 : 2 =_”). Each subtest contains eight blocks of five operations that are presented with increasing difficulty, and participants are asked to solve as many arithmetic facts as possible in a maximum of 60 s for each subtest. The total number of correct answers is considered. Higher scores reflect better outcomes and will be considered as an improvement.

Math Processing Task. This task is selected from the Psychology Experiment Building Language program (http://pebl.sourceforge.net/, accessed on 5 October 2021) [79,80,81], which measures the ability of children to approximately quantify the numerical magnitude of arithmetic information that is automatically retrieved from the long-term memory. Arithmetic facts (addition and subtraction) with single-digit numbers are presented at the center of a PC screen in horizontal format as a solution from left to right, followed by an equal sign (e.g., “8 + 1 =_”; “9 − 3 =_”). Participants are required to determine whether the result is less or greater than five by pressing the left shift key (for results less than five) or the right key on the keyboard (for results more than five). Several arithmetic facts are presented in 60 s, and participants are required to respond within 1500 milliseconds (ms).

At the end, the following data are automatically recorded: (a) accuracy of each response (0 = incorrect within 1500 ms or correct but after 1500 ms; 1 = correct within 1500 ms) and (b) reaction times (in ms) for each response. With regard to accuracy, higher scores indicate better outcomes and will be considered as an improvement. For speed, lower scores reflect better outcomes and will be considered as an improvement.

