### 2.2. Study Setting and Participants

Recruitment will take place at the Child and Adolescent Neuropsychiatry Unit of Bambino Gesù Children’s Hospital in Rome. Participants will be enrolled during the daily clinical activities of the I.Re.Ne Lab (Innovation Rehabilitation in Neurodevelopment Lab) by psychologists, neuropsychiatrists, and speech therapists. Should that be the case, participants will be selected retrospectively from a comprehensive database, upheld by the direction of the Head of the Unit ([name]), which encompasses several hundred patients who have been assessed according to the good clinical practices per international guidelines for neurodevelopmental disorders. Research assistants will contact the selected participants by phone and e-mail to determine their interest in the project.

All participants and their parents will be fully informed of the procedures and purpose of the experiment, and the principal investigator will obtain written consent prior to participant entrance into the study. Participation will be solely voluntary.

The inclusion criteria are as follows: (1) participants of both genders, diagnosed with MLD per the Diagnostic and Statistical Manual of Mental Disorders, Fifth Edition (DSM-5) [1] and national recommendations [69], confirmed by experienced developmental psychiatrists and psychologists through their developmental history and extensive clinical examination; (2) the mathematical total quotient (MTq), per the Diagnostic Battery for Developmental Dyscalculia, Second Edition (BDE-2) [70], at least two standard deviations (SDs) below the mean (composite score ≤ 70); (3) intelligence quotient (IQ) ≥ 85; (4) age between 8 years and 6 months and 14 years and 11 months inclusive; and (5) normal or corrected-to-normal vision.

The exclusion criteria are: (1) the presence of another primary psychiatric diagnosis (e.g., depression, anxiety), autism, or attention deficit hyperactivity disorder; (2) a personal history of neurological/medical/genetic diseases; (3) a personal history or first-degree-relative history of epilepsy; (4) having undergone neuropsychological treatment for MLD in the year before the baseline screen; and (5) receipt of a CNS-active drug treatment.

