### 2.3. Design, Randomization, and Blinding

The study will use a between-subject, randomized, double-blind, and sham-controlled design.

The screen for clinical eligibility will be completed on Day 0 of the trial, before the stratified randomization. Randomization occurs immediately after a participant completes the screening assessment, ensuring concealment of allocation. Participants will be allocated randomly to the following conditions: (1) Frontal Group (active tRNS over bilateral dlPFCs + cognitive training); (2) Parietal Group (active tRNS over bilateral PPCs + cognitive training); and (3) Sham Group (Sham tRNS over bilateral dlPFCs/PPCs + cognitive training). An independent researcher will perform the stratified randomization. The stratified randomization will use the minimal sufficient balancing method to prevent imbalances in baseline and will be based on the participants’ demographics (e.g., age, IQ, gender) and MTq [70].

The investigators who assess the participants will be blinded to the allocation, as will the participants and their parents. An independent researcher will maintain the randomization information until the data collection is completed. An emergency code break envelope will be provided to the principal investigator and will only be opened in the case of an emergency, such as a serious adverse event that requires knowledge of the interventions to manage the participant’s condition.

A baseline assessment (see Figure 1) will be completed on Day 1 (T0), before the interventions are administered. Participants will undergo combined interventions for 10 days (5 consecutive days per week for 2 consecutive weeks: from Day 1 to Day 5 and from Day 8 to Day 12). To minimize the influence of intracircadian variations, participants will attend stimulation sessions each day at the same time. Participants will also complete an assessment at the end of the interventions (Day 12, T1), 1 week later (Day 19, T2), and 3 months later (Day 102, T3). At the last follow-up, after the assessment, participants will be asked to guess their stimulation condition by the principal investigator.

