### 3.2. Statistical Analysis

The Shapiro–Wilk test will be used to test the normality of the data, and Levene’s test will be performed to analyze the homogeneity of the variances. When the data are normally distributed and the assumption of homogeneity is not violated, parametric analyses will be computed. When one assumption is not met, nonparametric tests will be conducted or log-transformation of the distribution will be applied, if appropriate. When appropriate, sphericity will be verified by Mauchly’s sphericity test. When sphericity is not met, Greenhouse–Geisser correction will be applied.

Chi-square analysis will be used to compare groups with regard to demographics, blindness, and safety measures (categorical variables).

Linear mixed-effects models, which account for within-subject correlations more optimally than analysis of variance and automatically handle missing values, allowing maximum use of available data [93], will be run to compare groups for primary (continuous variables: number line subtest) and secondary outcomes (continuous variables: arithmetic, neuropsychological, and psychological measures). The R package lme4 v1.1–17 [94,95], which estimates model parameters using restricted maximum likelihood estimation and computed *p*-values per Satterthwaite’s method [96], will be used. The linear mixed-effects models will include Group (Frontal, Parietal, and Sham) and Time (T0, T1, T2, T3) as fixed factors and Participants as the random factor. Baseline performance will be included as a covariate in our model, because it allows us to make better adjustments for minor differences in pretreatment means. The same analysis will be performed for the training accuracy data, including Group (Frontal, Parietal, and Sham) and Day (from 1 to 10) as fixed factors and participants as the random factor.

Pearson’s correlation will be used to determine whether and the extent to which arithmetic improvements are related to changes in neuropsychological measures, psychological measures, and spectral power of EEG frequency bands at T1, T2, and T3 (from T0).

The statistical results will be corrected for multiple comparisons by Bonferroni’s correction where appropriate.

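### The primary model adjusts only for T0, although screening very probably yields a second pre-treatment Number Line score that could add some precision

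*Protocol article*

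**What the plan says.** All references are to the Protocol article.

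- Section 2.5.1: "The primary outcome of the study will be the Number Line subtest of BDE-2". On the battery itself: "The battery encompasses several subtests that, in turn, are divided into three main quotients", with the MTq as the overall index.
- Section 2.2 requires an MTq of 70 or below for entry. It also allows that "participants will be selected retrospectively from a comprehensive database".
- Section 2.3: "The screen for clinical eligibility will be completed on Day 0 of the trial, before the stratified randomization". MTq is one of the variables used to balance the allocation. The baseline assessment is a separate step that "will be completed on Day 1 (T0), before the interventions are administered".
- Section 2.5: "the outcome measures will be presented to each participant individually at T0, T1, and each follow-up (T2 and T3"), which includes Number Line.
- Section 3.2 fits a linear mixed model with Group, Time (T0 to T3) and a random participant effect, and adds: "Baseline performance will be included as a covariate in our model". No screening score or MTq appears in the model. A Group-by-Time term is not spelled out.
- Section 3.3 states the primary hypothesis as active groups against Sham at T1, persisting at T3.

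**The concern.** A child cannot be declared eligible or be allocated without a scored BDE-2, and Number Line is a BDE-2 subtest. If the eligibility testing and the T0 testing are separate administrations, each child has two Number Line scores from before treatment, and the primary model uses one. A single subtest score carries occasion-to-occasion error. A second score on the same subtest is a strong candidate for an additional baseline covariate, and MTq is no full substitute because it is a broad composite.

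What is at stake is the width of the intervals for the active-versus-Sham contrasts. The trial is sized for a small effect (f = 0.15), and a 30% loss from the 102 recruited leaves 102 × 0.7 ≈ 71 children against the 78 said to be needed, so spare precision would be useful.

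**Working it through.** **1. Inputs.** From section 2.6: f = 0.15, α = 0.05, 80% power, 3 groups, 4 measurements, N = 78 (26 per group). The article gives no reliability, SD or correlation for Number Line, so every correlation below is an assumption.

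**2. The plan's own figure.** For the within-between interaction of a repeated-measures ANOVA, λ = f²·N·m/(1−ρ) with df (k−1)(m−1) = 6 and (N−k)(m−1) = 225. With ρ = 0.5 and sphericity, λ = 0.0225 × 78 × 4/0.5 = 14.04 and power is 0.801, so 78 is reproduced. ρ = 0.4 would give 93 and ρ = 0.6 would give 63. The sample size thus appears to rest on the Group-by-Time interaction with ρ = 0.5.

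**3. One or two baselines at a single visit, equal correlations.** In units of the outcome variance, the residual variance is 1 − r² with one baseline and 1 − 2r²/(1+r) with two.

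| r | one | two | cut | 80% power becomes |
|---|---|---|---|---|
| 0.5 | 0.750 | 0.667 | 11% | 84.4% |
| 0.6 | 0.640 | 0.550 | 14% | 85.6% |
| 0.7 | 0.510 | 0.424 | 17% | 86.7% |
| 0.8 | 0.360 | 0.289 | 20% | 87.8% |

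**4. Less favourable patterns.** Scores a day apart may agree better than scores weeks apart. With baseline-outcome correlation 0.5 and Day 0–Day 1 correlation r, the two-baseline residual is 1 − 2(0.25)/(1+r). For r = 0.7, 0.8, 0.9 and 0.95 the cut is 5.9%, 3.7%, 1.8% and 0.9%. At 3.7%, 80% power becomes 81.5%.

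For an older screening score, write a for the T0–outcome correlation, b for screening–outcome and r for T0–screening. The explained share is (a² + b² − 2abr)/(1 − r²). With a = 0.5:
- b = 0.4, r = 0.5: (0.25 + 0.16 − 0.20)/0.75 = 0.28, so 0.75 falls to 0.72, a cut of 4%.
- b = 0.3, r = 0.6: (0.25 + 0.09 − 0.18)/0.64 = 0.25, so there is no cut.

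**5. Which contrast gains.** Take 26 per group, unit variance and all correlations 0.6.
- *Group-by-Time, change from T0, T0 in the response:* SE = √(2 × 2(1 − 0.6)/26) = 0.248. A covariate that is constant over time cancels out of a change. Simulation gives 0.248 with and without the screening score. With about 30% dropout the SE moves only from 0.272 to 0.271 at T3.
- *Adjusted difference at a visit, T1–T3 as response:* √(2 × 0.64/26) = 0.222 with T0 alone and √(2 × 0.55/26) = 0.206 with both (simulated 0.221 and 0.205). If Day 0 and Day 1 correlate at 0.8, the two-baseline residual is 1 − 0.72/1.8 = 0.60 and the SE is 0.215, a fall of about 3%.
- *Adjusted difference at a visit, T0 also left in the response:* the simulated SE falls from 0.198 to 0.188, but these figures flatter the model. The pooled slope on T0 is (1 + 3 × 0.6)/4 = 0.7. That leaves residual variance (1 − 0.7)² = 0.09 at T0 and 1 − 2(0.7)(0.6) + 0.49 = 0.65 at each later visit. The model averages them to (0.09 + 3 × 0.65)/4 = 0.51, hence √(2 × 0.51/26) = 0.198. The real figure at a follow-up visit is √(2 × 0.65/26) = 0.224.

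Moving from change-from-T0 to T0 as covariate only (0.248 to 0.222) is therefore the larger step. The screening score adds a smaller one (0.222 to 0.206 at best under these assumptions).

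**The case against.** The case on the other side is strong in four respects.

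- **The plan is not in error.** Adjusting for one baseline is standard, and under randomization error in a baseline covariate costs precision only. A reader might infer that the group comparison is distorted by measurement error in T0. The article does not support that. This point stands in full.
- **The second score is inferred.** Number Line is not named as a component of MTq. A screen completed on Day 0 need not mean that the BDE-2 was given that day, or separately from T0. Children found through the database may have older scores. A reader might take it as settled that every child has a Day 0 Number Line score, but the documents make it only very probable that a separate pre-randomization score exists, of unknown age for some children.
- **In the model as written the covariate may do nothing.** Step 5 bears this out for the Group-by-Time interaction, which is also the test that reproduces N = 78. The power figures in step 3 therefore cannot be read as gains on the plan's own sample-size calculation.
- **A new covariate can lose children.** The mixed model copes with missing outcomes, but lme4 by default drops rows with a missing covariate. A child with only an MTq on file would leave the primary analysis.

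None of this removes the point. Section 3.2 itself states the covariate, and section 3.3 asks for active against Sham at particular visits, a contrast that does gain once T0 is taken out of the response. The objections limit the size and dictate the form of the remedy.

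**Conclusion.** This holds as an inexpensive precision improvement, not as a bias, contradiction or error. It depends on the sponsor confirming that a Number Line score from the eligibility BDE-2 is recorded separately from T0.

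The size is uncertain. The reduction in single-visit residual variance lies between about 0 and 20%: the upper end needs equal correlations near 0.8, and the low single figures apply if Day 0 and Day 1 correlate very highly or the screening score is old. Intermediate patterns fall between; for example, outcome correlation 0.7 with Day 0–Day 1 correlation 0.8 gives 1 − 0.98/1.8 = 0.456 against 0.510, a cut of 11%. A second score reduces the effect of baseline error and does not eliminate it. The interaction gains nothing while T0 remains a level of the response.

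**What to change.** First confirm that the subtest score from the eligibility BDE-2 is kept, in the same metric as T0, and with its test date. Then, in section 3.2, for the primary outcome and before unblinding:

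1. Make T1, T2 and T3 the response, and use T0 as a covariate only.
2. Add the screening Number Line score as a second covariate with its own coefficient. Do not average it with T0, because the screening BDE-2 was used to select children and is open to regression to the mean and practice.
3. Cross both covariates with visit, and name the adjusted active-versus-Sham difference at each visit as the estimate.
4. Where the screening subtest score is missing, impute it from pre-randomization information only, for example the mean plus a missing indicator, so that no child is dropped.

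The cost is wording, a few degrees of freedom (three for the added covariate crossed with three visits, plus any missing indicator) and an imputation rule. No new data, visits or participants are needed. If the screening subtest score proves not to be recorded, omit items 2 and 4; item 1 is still worth making.

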#### 2.5.2. Neuropsychological Measures

N-back [82] is a working memory task that comprises two conditions: visual-spatial and verbal. The visual-spatial condition consists of a series of visual stimuli (black boxes) in a certain location on the screen. After a training phase, participants are required to indicate whether the location of each box is the same as that of the box that immediately preceded it (level: 1-back). When the accuracy becomes greater than or equal to 80%, the evaluator will increase the difficulty of the n-back (for example, advancing from 1-back to 2-back). Similarly, the verbal condition entails listening to a continuous stream of letters. After a training phase, participants are required to decide whether each letter matches the letter that was heard immediately before (level: 1-back). When the accuracy becomes greater than or equal to 80%, the evaluator will increase the difficulty of the n-back (for example, progressing from 1-back to 2-back).

For both conditions, 35 trials with an interval between stimuli of 3.20 s will be presented. The number of correct answers and errors is considered and will be used to calculate the accuracy percentage on each level of n-back. Higher scores indicate better outcomes and will be considered as an improvement.

Geometric Puzzle. This subtest, as part of the NEPSY, Second Edition [83], measures mental rotation abilities in children and adolescents aged 3 to 16 years. A grid that contains several blank geometric figures in the center of the page is shown with a number of black geometric figures at the bottom. Participants are asked to pair two of the black figures to the two blank figures inside of the grid in a maximum of 45 s. First, participants are given instructions for the test and two practice items. Mental rotation abilities are necessary when the same figures inside and outside of the square are not in the same position, one of which has been rotated. The number of correct answers is recorded, and the raw score is converted into a weighted score. Higher scores reflect better outcomes and will be considered as an improvement.

#### 2.5.3. Self-Administered Psychological Questionnaires

Mathematics Anxiety Rating Scale-Revised (MARS-R), Italian adaptation. The Italian adaptation of the MARS-R [84] is a self-administrated questionnaire that is composed of 30 items that measures 3 main areas: learning math anxiety, math evaluation anxiety, and school anxiety. Participants are asked to read each item (e.g., “observe a professor working on the blackboard on an algebraic equation”) and indicate his level of anxiety on a Likert scale from 1 (low) to 4 (high). The raw scores are converted into z-scores. Lower scores indicate better outcomes and will be considered as an improvement.

Ability and motivation to study (Test AMOS 8-15). This battery measures strategies and motivation to learn in students aged 8 to 15 years to identify dysfunctional attitudes. It is based on a multicomponent metacognitive model [85] and considers a complex set of relationships that exist between metacognitive, strategic, cognitive, and emotional-motivational factors that collectively determine the level of academic achievement. The battery is composed of five questionnaires as follows: (1) Study Approach Questionnaire (QAS); (2) Questionnaires on Utility and Use of Strategies study (QS1 and QS2); (3) Study tests (PS); (4) Belief Questionnaires (QC1I, QC2F, QC30); and (5) Attributions (QCA). Each questionnaire can be administered alone or combined with others. In this study, only QAS, QC1I, and QC2F will be considered.

QAS is composed of 49 items, 7 each for 7 areas: motivation, organization, personal development, study flexibility, concentration, school anxiety, and attitude toward school. Participants are asked to read each item (e.g., “I like studying to learn new things”) and express their level of agreement on a Likert scale from 1 (not very true) to 3 (very true). QC1I comprises 4 items and evaluates personal beliefs on intelligence (static intelligence vs. modifiable intelligence). Participants are asked to read each item (e.g., “Your intelligence is something about you that you can not change”) and express their level of agreement on a Likert scale from 1 (not very true) to 3 (very true). QC2F is composed of three items and assesses personal beliefs with regard to their intellectual level or abilities/personality. Participants are asked to read each item (e.g., “I usually think I’m smart”) and express their level of agreement on a Likert scale from 1 (not very true) to 3 (very true). 

For all questionnaires, raw scores are converted into z-scores. Higher scores indicate better outcomes and will be considered as an improvement.

